Although the treatment with artesunate compared to quinine considerably reduces mortality in severe and cerebral malaria, the case fatality rate remains high at between 20% and 30%[[1]](#endnote-2). Improved supportive care can importantly further reduce mortality; a series from a well equipped intensive care unit in Paris showed a mortality of 11% in patients with severe malaria[[2]](#endnote-3). Supportive treatments include highly technical aids like renal replacement therapy and mechanical ventilation, but also easier to achieve treatments like enteral feeding. In the well equipped intensive care setting early start of enteral feeding in a wide variety of patients, including those with sepsis, is now common practice. Nutrition supplies vital cell substrates, antioxidants, vitamins, and minerals, essential for normal cell function. Studies have shown that early enteral feeding preserves the barrier function of the gut, has positive effects on immune functions, is associated with a decrease in hypermetabolism and organ failure, and reduces the chance of bacteraemia [[3]](#endnote-4) [[4]](#endnote-5) [[5]](#endnote-6) [[6]](#endnote-7) [[7]](#endnote-8) [[8]](#endnote-9). In severe malaria, patients are often poorly nourished and hypoglycaemia is a common complication, especially in patients receiving quinine. Also, bacteraemia with Salmonella species is more common in severe malaria[[9]](#endnote-10), associated with increased bacterial translocation in the gut. Enteral feeding might have a beneficial effect here. The downside of starting enteral feeding in the dependent comatose patient is the risk of aspiration pneumonia; this risk is also present in the mechanically ventilated patient[[10]](#endnote-11) [[11]](#endnote-12), although the risk is lower with the use of post-pyloric enteral feeding tubes[[12]](#endnote-13) [[13]](#endnote-14) [[14]](#endnote-15). A supine position of the patient is a risk factor[[15]](#endnote-16). Routine endotracheal intubation to protect the airway in comatose malaria patients is not a feasible option in most of the tropical countries where malaria is endemic. The use of enteral feeding through a naso-gastric (NG) tube might thus induce a much higher risk of aspiration pneumonia, outweighing the theoretical benefits.

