*General care measures for the patient with cerebral malaria will include:*

Head tilt position (15 to 30). Recording of GCS, blood pressure, respiratory rate, temperature, and oxygen saturation (pulse-oxymetry) every **4 hours.** Maintenance of an open airway, if needed, with a Guedel. Nursing on the side with turning every **2 hours** by the patient’s relatives to prevent bed sores. Catheterization of the bladder (Foley catheter) and recording of fluid input/output. Eye care with moisturizing eye ointment in the case of open eyes. Anti-pyretics: in case of fever, paracetamol 1g for adults and 15 mg/kg for children under 12 years will be given unless contra-indicated (liver failure). Once conscious and taking oral feed patients should be followed-up once daily.

*Investigations*

On admission a 10 ml blood sample will be taken for parasitaemia, complete blood count (CBC), including leukocyte differentiation and percentage of band form neutrophils, venous pH*, bicarbonate* and blood standardized base excess*, glucose*, electrolytes*, blood urea nitrogen*. (Parameters marked with * will be measured by i-STAT, using the EC8+ cartridges).

Peripheral blood parasitaemia and staging in thin film will be assessed on admission, followed by 12 hourly sampling until complete parasite clearance, defined by 2 consecutive negative peripheral blood slides.

Blood glucose will be checked 4 hourly until the patient regains consciousness. A blood glucose level below ≤2.8 mmol/l (50mg/dl) will be treated with 10% intravenous glucose (4 ml/kg body weight).

Blood count (i.e. total and differential white cell count, platelet count, haemoglobin and haematocrit), biochemistry and blood cultures will be repeated on indication. In particular, a blood count will be repeated when aspiration pneumonia or sepsis is suspected.

*Aspiration pneumonia*

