Aspiration pneumonia will be diagnosed clinically from history and chest examination (fever, respiratory distress, auscultatory crackles, oxygen saturation), and confirmed by chest X-ray (CXR). All patients will have a CXR upon admission. If possible, a CXR will be done in the radiology department of CMCH. If the patient is not transportable, a bed side CXR will be performed. The CXR will be repeated upon indication and 3 days after the first one for follow-up. Treatment will be with antibiotics (intravenous ceftriaxone in combination with metronidazole). Oxygen will be given by nasal cannula or face mask where indicated. In the case of severe respiratory insufficiency, a concerted effort will be made to transfer the patient to the intensive care unit of CMCH for mechanical ventilation.

Analysis

*Primary outcome measures include:*

1. Incidence of aspiration pneumonia.
2. Incidence of hypoglycaemia (<2.2 mmol/L).
3. Coma recovery time. The coma recovery time is defined as the time till a Glasgow Coma Score of 15/15 (BCS 5/5 in preverbal children).

*Secondary outcome measures include:*

1. Incidence of sepsis.

Sepsis is defined as the presence of infection (other than malaria) in combination with systemic inflammatory response syndrome (SIRS) as indicated by ≥ 3 of the following criteria: prolonged fever i.e. axillary temperature  38ºC or core temperature of  36ºC; a heart rate of  90 beats/min; a respiratory rate of  20 breaths/min (up to 5yrs 40) or the use of mechanical ventilation for an acute respiratory process; a white-cell count of  12 x 109/l or  4 x 109/l, or a differential count showing > 10% immature neutrophils.

2. Time to sit independently, which will be assessed daily.

3. Time to speak independently, which will be assessed daily.

4. Time to eat independently, which will be assessed daily.

5. Total duration (days) of admission in the hospital.

6. Survival. In hospital mortality will be recorded.

Sample size calculation

To detect an increase in incidence in aspiration pneumonia from 10% to 30%, a sample size of 124 (62 in each treatment group) is required. After this pilot study the data will be analysed. If early enteral feeding appears to be promising regarding a decrease in hypoglycaemia or a shortening of coma recovery times, not at the expense of a significant increase in aspiration pneumonia, a larger follow-up trial will be planned.

Randomisation

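### The secondary sepsis outcome can count aspiration pneumonia as its infection, so it overlaps the harm outcome and can mask or reverse an effect of early feeding on other infections; its heart-rate and respiratory-rate limits also fit children poorly

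*Protocol*

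**What the plan says.** The definition stands in the protocol under Analysis, Secondary outcome measures, item 1: "Sepsis is defined as the presence of infection (other than malaria) in combination with systemic inflammatory response syndrome (SIRS"). The second component is met "as indicated by ≥ 3 of the following criteria: prolonged fever", followed by heart rate, respiratory rate and white-cell count. The respiratory criterion can also be met by ventilation: "or the use of mechanical ventilation for an acute respiratory process". The heart-rate limit of 90 beats/min carries no age adjustment. The respiratory-rate limit of 20 breaths/min has a separate value of 40 up to 5 years only. Patients are eligible from 2 years of age.

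Incidence of aspiration pneumonia is primary outcome 1. The Aspiration pneumonia section bases the clinical diagnosis on "fever, respiratory distress, auscultatory crackles, oxygen saturation), and confirmed by chest X-ray (CXR"). It manages the condition as an infection: "Treatment will be with antibiotics (intravenous ceftriaxone in combination with metronidazole").

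The introduction gives, among the reasons for early feeding, that "early enteral feeding preserves the barrier function of the gut, has positive effects on immune functions", and also cites a lower chance of bacteraemia. Benefits of the study repeats the immune argument and sets it against a higher risk of aspiration pneumonia. On microbiology, Investigations says that "biochemistry and blood cultures will be repeated on indication", and its list of admission tests contains no culture.

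**The concern.** Sepsis is the only listed outcome that could show an effect of feeding on infections other than aspiration pneumonia. The definition removes malaria and nothing else, and no other text keeps aspiration pneumonia out. A patient with aspiration pneumonia therefore has the infection component, and the signs used for the diagnosis (fever, respiratory distress) lie close to two of the four SIRS groups. One further group would complete the definition.

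The protocol's own reasoning moves the two parts in opposite directions: more aspiration pneumonia with early feeding, fewer infections of other origin. A combined count nets one against the other. Early feeding could show as much sepsis as late feeding, or more, although it had reduced the infections that the rationale is about. What is at stake is the reading of one secondary outcome and of the infection mechanism.

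The limits for children add to this. A child of 6 is judged against 20 breaths/min and 90 beats/min. The protocol accepts that age matters but acts on it for one sign and one age band. Where a limit is set too low for a child's age, the SIRS component separates septic from non-septic children poorly, and it becomes easier for an aspiration pneumonia to qualify.

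**Working it through.** **The plan's own figure.** Sample size calculation gives 62 per group for 10% v 30% aspiration pneumonia, without alpha or power. With the pooled-variance formula, two-sided 5% and 80% power:

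n = [1.960 × √(2 × 0.20 × 0.80) + 0.842 × √(0.10 × 0.90 + 0.30 × 0.70)]² / 0.20² = (1.109 + 0.461)² / 0.04 ≈ 61.6, so 62 per group and 124 in all. The figure reproduces, and 10% v 30% is used below as the planning contrast.

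**Inputs**
- Aspiration pneumonia, late v early: 10% v 30% (Sample size calculation). 10% v 20% and 10% v 10% are added as milder cases.
- Other sepsis, late v early: 15% v 7.5%, a halving. Assumed; the protocol gives no sepsis rate.
- s, the share of aspiration pneumonias that meet SIRS: not in the protocol, so varied from 0 to 1 and taken as equal in both arms.
- Aspiration pneumonia and other sepsis taken as independent.

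**Formula.** All-cause sepsis = 1 − (1 − other sepsis) × (1 − s × aspiration pneumonia rate). For example, at 10% v 30% and s = 1: late 1 − 0.85 × 0.90 = 23.5%; early 1 − 0.925 × 0.70 = 35.3%.

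| Aspiration pneumonia, late v early | s | Sepsis, late | Sepsis, early | Early minus late, points |
|---|---|---|---|---|
| kept out of sepsis | 0 | 15.0% | 7.5% | −7.5 |
| 10% v 30% | 0.25 | 17.1% | 14.4% | −2.7 |
| 10% v 30% | 0.50 | 19.3% | 21.4% | +2.1 |
| 10% v 30% | 1 | 23.5% | 35.3% | +11.8 |
| 10% v 20% | 0.50 | 19.3% | 16.8% | −2.5 |
| 10% v 20% | 1 | 23.5% | 26.0% | +2.5 |
| 10% v 10% | 1 | 23.5% | 16.8% | −6.8 |

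**Share at which the benefit is cancelled**
- 10% v 30%: 0.85(1 − 0.10s) = 0.925(1 − 0.30s), so 0.1925s = 0.075 and s ≈ 0.39.
- 10% v 20%: 0.85(1 − 0.10s) = 0.925(1 − 0.20s), so 0.100s = 0.075 and s = 0.75.

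**Sensitivity to the assumed rate.** Keeping 10% v 30% and a halving of other sepsis, cancellation comes at s of about 0.26 when other sepsis is 10% in the late arm, 0.53 when it is 20%, and 0.81 when it is 30%.

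**What separating the two would buy.** With aspiration pneumonia kept out, power at 62 per group (two-sided 5%) to detect the halving is about 18%, 34% and 52% for late-arm rates of 10%, 20% and 30%. Separation removes the mixing but does not make sepsis a well-powered outcome.

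**The case against.** Several points on the other side are sound.

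- A reader might infer that the overlap could mislead the decision on a follow-up trial. The documents do not support that. The follow-up condition, under Sample size calculation, uses hypoglycaemia, coma recovery and aspiration pneumonia; the stopping rule, under Safety, uses aspiration pneumonia alone.
- A reader might infer that almost every aspiration pneumonia becomes a sepsis case. The protocol does not say so. SIRS needs three of four groups and prolonged fever, the pneumonia diagnosis sets no heart-rate or white-cell requirement, and respiratory distress is not the rate limit. Hence s is left open above.
- A reader might infer that malaria's own signs create sepsis cases. They cannot do so alone, because a second infection is required.
- Infection is one strand of the rationale, beside hypoglycaemia, energy supply and organ function. It is not the foundation of the trial.
- Masking is strongest at 10% v 30%, the contrast the trial is sized to detect. If that contrast is significant, it decides the matter whatever sepsis shows.
- All-cause sepsis is a legitimate, practical outcome, and aspiration pneumonia is reported separately. That does not fully answer the concern: two marginal rates do not show how many sepsis cases were aspiration pneumonias.
- Infection present on arrival is partly handled. Patients with features of aspiration pneumonia are excluded and all have an admission chest X-ray. Other infections present at entry should balance between arms in expectation, but the definition sets no onset condition.
- Sepsis without aspiration pneumonia has its own bias. If early feeding causes more aspiration pneumonia, more early-arm patients receive broad antibiotics, which may lower other infections in that arm. This argues against replacing all-cause sepsis, but not against showing the split.

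**Conclusion.** The overlap follows from the wording of the definition, and nothing in the protocol contradicts it. All-cause sepsis can mask or reverse an effect of early feeding on other infections. On the assumed 15% v 7.5%, the effect is cancelled once about 39% of aspiration pneumonias meet SIRS at 10% v 30%, or about 75% at 10% v 20%. Below those shares it remains visible but is diluted. These thresholds rest on the assumed sepsis rates, on independence and on an equal share s in both arms; only the 10% and 30% come from the protocol.

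The consequence is confined to interpreting a secondary outcome. Sample size, stopping rule and follow-up rule are untouched. The unadjusted heart-rate limit, and the respiratory-rate limit adjusted only up to 5 years, are a separate and smaller weakness of the same definition. This is an inexpensive improvement worth making.

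**What to change.** Keep all-cause sepsis as the listed outcome. Beside it, report by arm:
1. sepsis first arising after randomisation in which aspiration pneumonia is not the qualifying infection;
2. sepsis due to aspiration pneumonia.

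State how a patient with both is counted. Apply age-appropriate heart-rate and respiratory-rate limits to all children, extending what the protocol already begins for respiratory rate up to 5 years.

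The cost is definition wording and two table rows; no new procedure is needed. Heart rate is not among the listed four-hourly recordings, but the existing definition already depends on it.

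Three limits should be stated with the split. Events will be few and power low. The source will often be attributed clinically, because cultures are taken on indication and none is listed at admission. Antibiotics given for aspiration pneumonia may lower other infections unequally between arms. The split should therefore be presented as descriptive, not as a test of the infection mechanism.

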At Chittagong Medical College Hospital (CMCH), the current practice is to start early enteral feeding through a NG-tube, with a volume of 2-4ml/kg per feed every 2 hours, avoiding 2 late night feeds, resulting in a total of 10 feeds per day for adults. For children fluid supplementation is as follows: for age 2-4years: 100 - 120ml/kg/day; 4-8yrs 90-100ml/kg/day; 8-12yrs 70-90 ≥12 yrs 60-70ml/kg/day given every 2 hours round-the-clock. In both the cases the enetral feeding volume is derived from total volume subtracting the volume given as i.v. fluids. The feeds are prepared from locally available food by blending or commercially available powder form. Although not formally assessed, aspiration pneumonia is a rather common complication of NG feeding in CMCH. Factors that can contribute include the supine position of the patient and no check for gastric retention before the next feeding. We here propose a randomized trial to compare the start of early versus late nasogastric tube feeding, with aspiration pneumonia, incidence of hypoglycaemia and coma recovery times as primary outcome measures.

Materials and Methods

*Place and Period of Study*

It is planned to study 124 consecutive patients, age 2 y/o, with cerebral *Plasmodium falciparum* malaria, defined as a Glasgow Coma Score (GCS) below 11or BCS <3 (for pre-verbal children) and the presence of asexual stage *P. falciparum* parasites in a peripheral blood slide, admitted to Chittagong Medical College Hospital, Chittagong, Bangladesh. Patients will be recruited from the internal medicine wards (ward 13, 14, and 16) and from the paediatric ward.

*Inclusion Criteria*

1. Cerebral falciparum malaria defined as a GCS<11or BCS <3 (for pre-verbal children), and the presence of asexual forms of *P. falciparum* in the peripheral blood smear.
2. The attending relative able and willing to give informed consent.
3. ≥2 years of age

*Exclusion Criteria*

1. Relatives unable or unwilling to give informed consent.
2. Patients who already have the features of aspiration pneumonia.
3. Pregnancy
4. Diabetic requiring insulin
5. Contraindications to enteral feeding:

-Circulatory shock

-Mechanical bowel obstruction / ileus / ischaemic colitis (redcurrant jelly stools)

-Severe diarrhea (> 6 per 24 hours), severe vomiting (> 6 per 24 hours) or severe dehydration due to either

-Pancreatitis (laboratory confirmed: serum amylase >500 U/L)

6. Known allergies to artesunate or quinine

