7. Severely malnourished child (according to WHO criteria)

*Examination and Treatment*

On enrolment a full history and physical examination will be carried out. Nutritional status of the patient will be assessed by skin-fold thickness in the triceps region of the left arm and the mid upper arm circumference will be measured. Weight/height and presence of bilateral pedal edema (WHO criteria) for malnourished children will be assessed.

First line antimalarial treatment will be with intravenous artesunate, if available. Artesunate (Guilin No 2 Pharmaceutical Factory, Guangxi, Peoples’ Republic of China) will be given in a dose of 2.4 mg/kg body weight on admission, then at 12 hours, 24 hours, and thereafter once daily until oral medication can be taken reliably. Each 60 mg vial contains anhydrous artesunic acid which is dissolved initially in 1 ml 5% sodium bicarbonate and then mixed with 4 ml of 5% dextrose before injecting as a bolus into an indwelling intravenous cannula. When the patient has recovered sufficiently to take tablets, a full adult course of artemether-lumefantrine (CoartemR) will be given: 4 tablets twice daily for 3 days. Currently injectable artesunate is not registered yet in Bangladesh for the treatment of severe malaria. In case artesunate for injection is not available, the patient will be treated with i.v. quinine. A loading dose of 20 mg/kg will be given over 4 hours time followed by a dose of 10 mg/kg over 2 to 4 hours every 8 hours for a total of 7 days, or until the patient has recovered sufficiently to take tablets, in which case a full course of coartem will be given (see above). Patients will be managed in accordance with the World Health Organization guidelines 2006.

*Treatment allocation*

All patients will receive a NG tube. Patients will be randomized to either receive enteral feeding upon admission through the NG tube *(arm 1)*, or no feeding until able to take oral food or maximum until 60 hours (adults i.e. >12 years old) or 36 hours (children i.e. <12 years old) after admission followed by enteral feeding *(arm 2)*. The feed used in the study will be Revit-R/Renovit(patient with renal insufficiency) (Fasska SA, Louvain la Neuve, Belgium. The preparation comes as a powder, which will be dissolve in bottled water according to the instructions of the manufacturer (220g per liter water which will provide 1 kcal/ml) The feeding protocol is as follows:

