Check position of NG tube before start of the first feed with a large syringe and before subsequent feeds by checking the position of a mark drawn on the tube at the time of insertion. Position the patient in the head tilt position (head 15° above horizontal). Start NG feeding with 2-4 ml/kg feeding every 2 hours in adult 10 feeds per day; omitting 2 late night feeds, this will deliver1000-2000kCal per 24 hours for adults weighing 50 kg. For children, the volume of enteral feeding will be calculated from the total amount of fluids to be given per 24 hours as follows: for age 2-4years: 100 - 120ml/kg/day; 4-8yrs 90-100ml/kg/day; 8-12yrs 70-90 ≥12 60-70ml/kg/day. The enteral feeding volume is derived from this total volume subtracting the volume given as i.v. The total amount of enteral feeding in children is divided in 12 feeds, given every 2 hours round-the-clock

Gastric retention will be measured just before the next feeding. Gastric retention is defined as> 4 ml/kg in adult and >2/3rd of the 2 hours previous feed in children. If gastric retention is present: feeding is discontinued and prokinetic drugs domperidon suppositories are added for adults domperidon 20 mg suppositories, every 8 hours; for children: domperidone suppository 15mg 1/2 suppository up to 5 years & 1 suppository beyond 5 years. In adults retention is reassessed 4 hourly. If the retained volume is <4 ml/kg, discard this volume, and feeds are continued every 2 hours as before. In children retention reassessed 2hourly and if the retention is < 2/3rd of the previous 2 hours feed this volume discard it, and feeds are continued every 2 hours as before.

Adult patients in the control arm (delayed start of enteral feeding) will receive 50-60ml 5% DS (glucose-saline)/kg/24 hours. The energy contents the infusion fluid containing 50-60g dextrose per liter around 200 kCal per liter, so that the energy given is 10-12 kCal/kg/ 24 hours, or 500-600 kCal for the average 50 kg patient. Paediatric patients in the control arm (arm 2) will receive 10% Dextrose in half strength saline (10% dextrose in 0.45% NaCl) in the volumes as above. This contains 400kCal/L, so that daily total calories delivered to the children not receiving enteral feeding will be for 2-4 y/o: 40-48 kCal/kg, for 4-8 y/o: 36-40 kCal/kg and for 8-12 y/o: 24-28 kCal/kg.

Family members will be instructed in the techniques for checking NG tube position using a pre-drawn mark, checking for gastric retention and giving NG feeds.

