Randomisation will be balanced in blocks of 20 by computerized method using STATA statistical software package.

Safety

Current practice in CMCH is to start on the day of admission with enteral feeding. However, if the current study shows a significant increase in the incidence of aspiration pneumonia in the group receiving early enteral feeding, randomization will be stopped, and patients will only receive enteral feeding after regaining consciousness, or 60 hours after admission. Since aspiration pneumonia is an identified risk, interim analyses will be performed after every 50 patients included. Interim data will be analysed by the Data Safety Monitoring Committee.

Benefits of the study

There is currently equipoise about the benefit of the start of early enteral feeding in patients with cerebral malaria in the tropical setting. Theoretical advantages (prevention of hypoglycaemia, restoration of immune function, etc) are countered by the increased risk of aspiration pneumonia. The study has a clear practical goal to guide this important part of the treatment of patients with cerebral malaria.

Finance

Costs involved in the study will be financed by the Wellcome Trust of Great Britain

References

1. SEAQUAMAT study group. Artesunate versus quinine for treatment of severe falciparum malaria: a randomised trial. Lancet 2005; 366: 717-725 [↑](#endnote-ref-2)

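### A single printed block size of 20, with visible arms and a judgement-based exclusion, lets a tally reveal about 9% of assignments; the risk is modest and cheap to reduce

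*Protocol*

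**What the plan says.** The allocation method is given in one sentence of the protocol's Randomisation section: "Randomisation will be balanced in blocks of 20 by computerized method using STATA statistical software package". It names one block size and does not say that the size varies.

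Other sections bear on how far that sequence could be foreseen and used:

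- **Setting.** Patients are those "admitted to Chittagong Medical College Hospital, Chittagong, Bangladesh", and "Patients will be recruited from the internal medicine wards (ward 13, 14, and 16) and from the paediatric ward" (Place and Period of Study). The same section plans for consecutive patients.
- **Visibility of the arms.** "Patients will be randomized to either receive enteral feeding upon admission through the NG tube"; the other arm gets no feed for up to 60 hours (adults) or 36 hours (children) unless the patient can eat sooner (Treatment allocation). The feeding protocol adds: "Family members will be instructed in the techniques for checking NG tube position using a pre-drawn mark, checking for gastric retention and giving NG feeds". No masking is described. That the trial is open is an inference from these passages; the protocol does not use the word.
- **Exclusion 2.** "Patients who already have the features of aspiration pneumonia", with no thresholds.
- **Outcome.** "Aspiration pneumonia will be diagnosed clinically from history and chest examination", followed by X-ray confirmation. Every patient has an X-ray on admission, but its timing relative to randomisation is not given. Aspiration pneumonia is primary outcome 1. It also sizes the trial, enters the decision on a follow-up trial, and triggers stopping.

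**The concern.** Selection bias at enrolment needs three things: some ability to foresee the next arm, room for judgement about who is eligible, and a link between that judgement and the outcome. All three are present here. A known fixed block with visible past assignments supplies the first. Exclusion 2 supplies the second and third, since it concerns the condition that is later counted as the outcome.

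Suppose an enroller who expects the next place to be early feeding reads a borderline chest as already showing pneumonia, but enrols a similar patient when delayed feeding is expected. High-risk patients would then collect in the delayed arm and an increase under early feeding would be partly masked. The opposite preference would create an apparent increase. Patients turned away are never randomised, so the analysis cannot put this right afterwards.

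**Working it through.** **The plan's own figure.** Inputs from Sample size calculation: 10% v 30%, 62 per arm. The error rates are not stated; I assume two-sided 5% and 80% power, with pooled variance under the null and no continuity correction:

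n = [1.96·√(2·0.20·0.80) + 0.842·√(0.10·0.90 + 0.30·0.70)]² / 0.20² = (1.109 + 0.461)² / 0.04 ≈ 61.6, so 62 per arm and 124 in all.

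This reproduces the plan. Power at 62/62 is 80.3%.

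**Predictability of fixed blocks of 20** (m = 10 per arm, one list, all past arms and the block boundaries known).

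- Certain assignments per block: 2m/(m + 1) = 20/11 = 1.82, or 9.1%. The 124 patients make six full blocks plus 4 of a seventh. Those 4 cannot be certain, so the expected number is 6 × 1.82 = 10.9, about 11 of 124.
- Correct guesses per block when always naming the arm with more places left: m + (4^m / C(2m, m) − 1)/2 = 10 + (1,048,576/184,756 − 1)/2 = 10 + 2.34 = 12.34 of 20, or 61.7%. By simulation over 124 patients it is 61.4%. Chance is 50%.
- About 26% of assignments can be called at odds of 2:1 or better, and about 18 of 124 with at least 75% probability.

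**Correct guesses by tally under other schemes**

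| Scheme | Correct guesses |
|---|---|
| Fixed 20 | about 61% |
| Random sizes 12, 16, 20, 24, 28 | about 61% |
| Random sizes 10 to 20 in steps of 2 | about 63% |
| Random sizes 4, 6, 8 | about 68% |
| Unrestricted 1:1 | 50% |

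**Possible effect on the comparison.** The protocol gives no inputs for this, so these are assumptions: no true effect, 25% of candidates borderline, a 40% or 50% risk of aspiration pneumonia in them against 10% in the others, a perfect tally, and every borderline patient turned away whenever early feeding is the likelier next arm. Simulated shift in early minus delayed, in percentage points:

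| Scheme and behaviour | Shift |
|---|---|
| Fixed 20, full tally-based selection | about −1.7 to −2.3 |
| Fixed 20, half of borderline patients turned away | about −0.7 to −1.1 |
| Fixed 20, acting only when the next arm is certain | about −0.5 to −1 |
| Random sizes 12 to 28, full tally-based selection | about −1.7 to −2.3 |
| Unrestricted 1:1, same behaviour | about −0.5 to −0.6 |

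The residue in the last row comes from screening on the running tally in a finite sample; no guess beats 50% there. The standard deviation of the difference is about 7 points. Under full selection the chance of a falsely significant increase falls from a nominal 2.5% to about 1%.

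**Price of unrestricted allocation.** Averaged over Binomial(124, 0.5) arm sizes, power is 79.9% against 80.3%. The 95% limit for the difference in arm sizes is 1.96·√N:

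| Patients | Unrestricted, 95% limit | Fixed 20, worst case |
|---|---|---|
| 50 (first interim) | 1.96·√50 ≈ 14 | 10 (30 v 20) |
| 100 (second interim) | 1.96·√100 ≈ 20 | 0 |
| 124 | 1.96·√124 ≈ 22 | 4 (64 v 60) |

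**The case against.** The strongest reply is that 20 is already a long block and is harder to guess than the small varying blocks in common use. Using it would take a complete tally over four wards, a shared preference among enrollers, and a readiness to turn patients away improperly. The protocol commits to consecutive patients and gives every patient an admission X-ray. The inputs behind the 2-point shift are invented, and the trial calls itself a pilot. Most of this stands and sets the size of the point. The safeguards are only partial: exclusion 2 is applied within the consecutive series, and nothing requires the X-ray to be read before randomisation.

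Three stronger readings are tempting, and the documents do not support them.

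- **That the list is unconcealed or held on the wards.** The protocol is silent on who holds it and on when the arm is released. Silence is not a statement that concealment is absent, and such detail may sit elsewhere. The point rests on the stated block size: even a well-kept list can be tallied when past arms are visible and the size is known.
- **That harm from early feeding will be hidden.** The direction depends on the enroller's preference. The protocol describes aspiration pneumonia as fairly common with tube feeding at this hospital, but it also declares equipoise and says that early feeding is current practice.
- **That varying the block size cures the problem.** It removes the certain assignments. It does not reduce bias from tally guessing, as the equal shifts above show.

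**Conclusion.** The point holds as a modest weakness in a stated design choice. A fixed, printed block of 20 in a one-hospital trial with visible arms makes about 9% of assignments knowable (about 11 of 124) and about 61% guessable. The exclusion that could be bent to that knowledge concerns the primary outcome itself. Those figures assume one list and a complete tally. If each ward had its own list, which is not stated, tallying within a ward would be easier but fewer blocks would reach their predictable end.

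The consequence is much less certain than the predictability. About 2 points, against a 20-point design difference and a standard deviation of about 7, is the result of full selection on assumed inputs. It is not an estimate of what will happen. Priority is minor to moderate: the change is worth making because it costs little and because the bias could not be repaired later.

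**What to change.** Replace the fixed block size in the Randomisation section with one of these.

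- **(a) Long block sizes varied at random**, for example 12, 16, 20, 24 and 28, with the protocol saying only that sizes vary. This essentially removes the certain assignments and hides the block boundaries. Best-guess accuracy stays near 61%, so it does not reduce bias from tally guessing.
- **(b) Unrestricted 1:1 randomisation of the 124 patients.** This takes tally guessing to 50%. It costs about 0.4 points of average power, and arm sizes may differ by up to about 22 at the end (95% limit), with imbalance also possible at the interim looks. It is the stronger remedy if that imbalance is acceptable.

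Under either, state that eligibility, including the decision on exclusion 2, is recorded before the arm is released. Do not move to small varying blocks such as 4, 6 and 8: a tally guesses these about 68% of the time, worse than the present scheme.

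The cost is a short change to the protocol text and a regenerated list from the same software. The sample size stays at 124.
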